### Experimental condition: OneUS intervention app

The intervention app is a 5-week program comprising 11 training sessions specifically designed to cultivate and enhance and positive emotions (gratitude, hope, pride, love, and serenity) and positive thinking. The program includes one introductory session with educational content on positive emotions and positive thinking, five sessions to cultivate positive emotions and five sessions for training the skills necessary to create and maintain positive thoughts. Each week, the program will focus on simultaneously practicing a specific positive emotion and a positive thinking skill (refer to Table 1). These practices will include educational activities (such as psychoeducational videos and informational content), assessment questions (to evaluate knowledge about positive thinking and positive emotions), feedback exercises (including identifying, modifying, and cultivating positive thoughts and expressing positive emotions), and guided or self-administered practice (such as mindfulness and Love-Kindness Meditation). The app (OneUS) will monitor individual progress by tracking content consumption and exercise performance, and participants will receive notifications and messages as reminders to engage in each session.

**Table 1 tab1:** General content and weekly activities.

		Intervention weeks				
		Week 1	Week 2	Week 3	Week 4	Week 5
Positive emotions	Content	Gratitude	Authentic pride	Love	Hope	Serenity
	Daily practice	Counting blessings	Reflective meditation and self-affirmation messages	Loving-kindness Meditation	Brief Hope Intervention	Mindfulness exercise
Positive thinking	Content	Recognizing negative and positive thoughts	Turn negative thoughts into positive ones	Identify the positive aspects of everyday situations	Problem-management	Interrupting negative thoughts
	Daily practice	Journal of thoughts	Positive self-talk	Recording of experiences and positive thinking	Positive internal dialog	Best possible self

In the introductory session, information on the advantages of cultivating positive emotions and positive thinking will be presented (MacLeod and Moore, 2000; Kok and Fredrickson, 2013). In the first week, the practice of positive emotions will involve a daily exercise of counting blessings, where participants identify and record things, they are grateful for Boggiss et al. (2020). The positive thinking activity will involve acknowledging both positive and negative thoughts and documenting them in a journal.

In the second week, the practice of *positive emotions* will focus on cultivating authentic pride through reflective meditation and self-affirmation messages, which will increase awareness of accomplishments, motivations, and successful outcomes resulting from the participant’s actions (Hill et al., 2020). The *positive thinking* activity will involve learning how to turn negative thoughts into positive ones. The practice will involve strengthening of positive self-talk to organize thoughts, assign positive meanings, and engage in silent or verbal self-dialog (Santos-Rosa et al., 2022).

The third week will focus on cultivating *positive emotions* by introducing the concept of love - which can create a feeling of connection and motivation with oneself and others. Loving-kindness meditation (LKM) will be used to strengthen unconditional expressions of love and care for self and others, and to foster an altruistic desire for success, happiness, and a positive future for all (Zeng et al., 2015). The guided practice of LKM is based on a tool designed by Seppala et al. (2014). The *positive thinking* practice will focus on identifying the positive elements of situations or events of everyday life (e.g., accomplishing a goal, successfully completing an everyday task, recognizing a personal skill), regardless of whether they are favorable or adverse. Participants will keep a daily log of their experiences and recognize any positive thoughts around these events that arise naturally (Rice and Fredrickson, 2016).

During the fourth week, *positive emotion* practice will focus on cultivating hope through a condensed version of the Brief Hope Intervention (BHI) (Chan et al., 2010). The BHI will be adapted to a virtual environment to promote hopeful internal dialogs about goals (goal setting), pathways to reach goals, and strategies to overcome obstacles (Snyder et al., 2000). The *positive thinking* activity will consist of learning to manage problems by breaking them into smaller parts and creating a positive internal dialog about each part (Naseem and Khalid, 2010).

In the fifth week of the program, the practice of *positive emotions* will encompass the cultivation of serenity, with a guided mindfulness exercise to become aware of current favorable or difficult situations and elicit feelings of peace and acceptance of the experiences evoked (Zoellner et al., 2007). The *positive thinking* practice will consist of interrupting negative thoughts through relaxation exercises. These exercises will include brief guidance on abdominal breathing, progressive muscle relaxation, and Mindfulness (Toussaint et al., 2021). In addition, there will be a guided practice of the best possible self, which will contain visualization exercises of oneself reaching one’s full potential and generating positive thoughts from this (Carrillo et al., 2019).

### Active control condition

The comparator will be an active control condition. Participants in this condition will be trained in mental imagery exercises in normal everyday life situations. This condition will be considered an active control because the participants will perform mental imagery of neutral events and emotion monitoring. The app design for this condition will have the same structure as the experimental condition and will include a user profile, menu, assessment measures, and notifications.

## Outcome measures

The outcome measures will be completed at 8 time points: baseline (t1), intervention (t2, t3, t4, t5, t6) post-intervention (t7), and 3-month follow-up (t8), following the recommended timeline outlined in the SPIRIT 2013 statement (refer to Table 2). The SPIRIT 2013 statement serves as a checklist for clinical trial protocols, offering guidelines on the essential content and a standardized diagram of activities, interventions, and measures (Chan et al., 2013).

**Table 2 tab2:** Schematic diagram for timeline participant.

	Enrolment	Baseline	Intervention					Close-out	Follow-up
TIMEPOINT	*0*	*t1*	Week 1 (t2)	Week 2 (t3)	Week 3 (t4)	Week 4 (t5)	Week 5 (t6)	*t_7_*	*t8*
Enrolment:									
Eligibility screen	X								
Informed consent	X								
Allocation	X								
Interventions:									
Training and daily practice of positive emotions and positive thinking									
Active control									
Assessments:									
Socio-demographic characteristics	X								
Well-being		X	X	X	X	X	X	X	X
Optimism		X	X	X	X	X	X	X	X
Hope		X	X	X	X	X	X	X	X
Subjective Happiness		X	X	X	X	X	X	X	X
Stress		X	X	X	X	X	X	X	X

## Primary outcome

### Well-being

Well-being will be assessed with the PERMA-profiler Scale (Butler and Kern, 2016). This scale evaluates well-being across five dimensions: Positive Emotions, Engagement, Relationships, Meaning, and Accomplishment. Additionally, it includes measures for physical health, negative emotions, loneliness, and overall happiness. The scale consists of 23 items on an 11-point scale, that are scored by calculating the arithmetic mean. The closer the mean is to 11, the higher the levels of well-being. The PERMA-profile was adapted and validated for use in the Brazilian population using a sample of 1,327 adults. The results indicated reliable indices for the overall PERMA factor (Guttman λ6 = 0.94 and McDonald Ω = 0.94), and for each individual dimension: Positive Emotion (λ6 = 0.86 and Ω = 0.90), Engagement (λ6 = 0.52 and Ω =. 62), Relationships (λ6 = 0.71 and Ω = 0.78), Meaning (λ6 = 0.80 and Ω = 0.86), and Accomplishment (λ6 = 0.76 and Ω = 0.81) (De Carvalho et al., 2021).

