**Methods:**

The study is designed as a randomized controlled trial. Two hundred participants will be randomly assigned to either a mobile health intervention condition (OneUS App) or an active control condition. The intervention consists of a program to cultivate positive emotions and positive thoughts. The active control intervention will comprise a set of mental imagery exercises and daily routine recording. The primary outcome comprises optimal well-being assessed using the multidimensional PERMA-Profiler scale. The sample will include adult people from the general population, who will be assessed at 8 time points: baseline (t1), intervention (t2, t3, t4, t5, t6) post-intervention (t7) and 3-month follow-up (t8).

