#### Optimism

Optimism will be assessed with the Life Orientation Test (LOT-R). The LOT-R is a self-report test that uses a Likert scale to measure optimism as a single trait. The test comprises 10 items, with six items formulated positively (items 1, 4, 10) and negatively (items 3, 7, 9), and four distractor items (2, 5, 6, 8). Participants are required to indicate their level of agreement with each item on a 5-point scale, where 1 represents “strongly disagree” and 5 represents “strongly agree.” The total score can range from 6 to 30. To calculate the score, the values of the negative elements are reverse scored and then added to the values of the positive elements, with higher scores indicating greater optimism. The LOT-R was adapted and validated for use in the Brazilian population using a sample of 844 adults and showed adequate internal reliability indices, with an alpha of 0.80 (Bastianello et al., 2014).

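### As written, the primary well-being score is the mean of all 23 PERMA-Profiler items with higher read as better, although the scale includes negative-emotion and loneliness measures and no reversal or exclusion is stated.

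*Protocol article*

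**What the plan says.** The abstract leaves the primary score general: "The primary outcome comprises optimal well-being assessed using the multidimensional PERMA-Profiler scale". The Well-being section under Primary outcome then makes four statements in sequence.

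- Content: "This scale evaluates well-being across five dimensions: Positive Emotions, Engagement, Relationships, Meaning, and Accomplishment".
- Further content: "Additionally, it includes measures for physical health, negative emotions, loneliness, and overall happiness".
- Scoring: "The scale consists of 23 items on an 11-point scale, that are scored by calculating the arithmetic mean".
- Direction: "The closer the mean is to 11, the higher the levels of well-being".

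Reliability follows: "The results indicated reliable indices for the overall PERMA factor (Guttman λ6 = 0.94 and McDonald Ω = 0.94", and then values for each of the five dimensions. None is given for a mean over 23 items. The paragraph does not say how many items measure negative emotions or loneliness, whether they are reversed, or whether any items are left out.

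The Optimism section, by contrast, spells out the keying of the LOT-R: "the values of the negative elements are reverse scored and then added to the values of the positive elements". It also lists which LOT-R items are distractors.

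**The concern.** The scoring sentence takes the 23 items as its subject, and the next sentence reads a single mean in a single direction. If items on negative emotion and loneliness enter that mean unreversed, a participant who becomes less lonely or less distressed loses points on the primary outcome. The hypothesis at the end of the Introduction is that the app raises well-being and lowers psychological distress, so these are items that the intervention could plausibly move.

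This is the only primary outcome, and Table 2 schedules it at all eight time points. An analyst who follows the section literally computes a score that mixes opposite directions. An analyst who does not follow it must choose a score that the article never names.

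**Working it through.** **Consistency check (needs no assumed item count beyond at least one negative item).** The direction sentence says that approaching the top means more well-being. If even one unreversed negative item is in the mean, the top is reached only when that item is also at its maximum. The scoring sentence and the direction sentence then cannot both hold. The top value of 11 is also reachable only if the 11 points are coded 1 to 11. Under 0 to 10 coding no mean can reach it, and the article does not say which coding applies.

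**Inputs.** From the Well-being section: 23 items, 11 response points. Not given, so assumed: m = 3, 4 or 5 negatively keyed items. The article offers no figure of its own to reproduce on this point.

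**Best attainable mean** (best answer on every item, no reversal):

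- 1 to 11 coding: ((23 − m) × 11 + m) / 23 = 9.70, 9.26, 8.83 for m = 3, 4, 5.
- 0 to 10 coding: (23 − m) × 10 / 23 = 8.70, 8.26, 7.83.

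**Share of the raw shift kept.**

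- The app shifts every item by the same amount in its favourable direction: (23 − 2m) / 23 = 17/23, 15/23, 13/23 = 74%, 65%, 57%. This is partial offset.
- The app shifts the other items equally and leaves the negative ones unchanged: (23 − m) / 23 = 20/23, 19/23, 18/23 = 87%, 83%, 78% of the shift per moved item. This is dilution only.

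**Share of the standardised effect kept.** The raw figures overstate the loss when negative and positive items are inversely correlated, because the unreversed mean then also has a smaller variance. Assume equal item variances, correlation r within each block of items, correlation −ρ between the blocks, and the equal favourable shift above. Relative to a correctly reversed 23-item mean, the ratio is

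((23 − 2m) / 23) × √[(A + C) / (A − C)],

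with A = 23 + r[(23 − m)(22 − m) + m(m − 1)] and C = 2ρm(23 − m).

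- ρ = 0: C = 0, so the ratio equals the raw share: 0.74, 0.65, 0.57.
- r = ρ = 0.5, m = 3: A = 216, C = 60; 0.739 × √(276/156) = 0.98.
- r = ρ = 0.5, m = 4: A = 200, C = 76; 0.652 × √(276/124) = 0.97.
- r = ρ = 0.5, m = 5: A = 186, C = 90; 0.565 × √(276/96) = 0.96.

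With r from 0.3 to 0.5 and ρ from 0 to r, the standardised effect kept is therefore 0.74 to 0.98 (m = 3), 0.65 to 0.97 (m = 4) and 0.57 to 0.96 (m = 5). The loss runs from about 2% to 43%, depending on quantities that the article does not give.

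I do not carry this through to power. The Sample size section states no effect size, standard deviation or correlation between time points, so any power figure would rest on further assumptions.

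**The case against.** The strongest reply is that the scoring sentence is loose prose in a condensed article and not an algorithm. It does not expressly say that all 23 items go unreversed into one mean. Well-being is tied to five dimensions, the other measures are introduced as additions, the direction sentence makes sense only if negative items are left out or reversed, and reliability is quoted only for PERMA scores. All this suggests that a PERMA-only or correctly keyed score was intended. The contrast with the LOT-R is also limited evidence, since scoring detail varies across the article: the Hope section sums the ratings over all items although it names four of the twelve as distractors.

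Much of this stands as evidence of intent. A reader might infer from the scoring sentence that the trial will certainly mis-score its primary outcome. The text does not prove that. But the reply does not rescue the text. If a PERMA-only score is meant, the 23-item sentence is wrong and no single primary score is named. If a reversed 23-item score is meant, the rule lacks the step that gives it its direction. Nor is this detail left to a fuller document: the article chose to state the rule, and the rule conflicts with the sentences around it.

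A reader might also want to say that the rule departs from the published Brazilian scoring or from other trials. The article describes neither, so that argument is not available. What can be said is that the rule does not match the scores whose reliability the article itself reports.

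**Conclusion.** Wrong as written. Followed literally, the stated rule lets worse negative emotion and loneliness raise the primary score. It contradicts the stated direction of that score, and it is not the score for which reliability is quoted.

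A reader might infer that the treatment effect is partly cancelled. That is not established. It requires that the literal rule is applied and that the app lowers the negative items; if the app does not move them, the effect is only diluted. The 74% to 57% retention rests on 3 to 5 negative items and an equal favourable shift on every item, both assumed. On the standardised scale the loss may be as small as 2% to 4%. The contradiction in the text depends on none of these figures.

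**What to change.** Replace the 23-item rule with one named primary score: the overall PERMA score, formed from the items of the five PERMA dimensions, with those items listed. Report negative emotions, loneliness and physical health separately as secondary outcomes, and say where the overall-happiness measure belongs. If the negative items are to stay in the primary score, state that they are reversed before averaging. State the actual coding of the 11 response points (0 to 10 or 1 to 11), and describe the top of the score accordingly in place of the present reference to 11.

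The cost is wording in the protocol and the analysis plan, plus scoring code. The item responses are collected in any case, so no new data are needed. The change should be made before the analysis begins, so that the choice of score is fixed without sight of the results.

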### Secondary outcomes

#### Perceived stress

The perception of stress will be evaluated with the Perceived Stress Scale (PSS-10). This scale evaluates whether a person perceives everyday situations as stressful (Cohen et al., 1983). It consists of 10 items with response options that range from “Never” to “Very often,” higher scores indicate greater perceived stress. The PSS-10 was adapted and validated for use in the Brazilian population using a sample of 793 adults and showed adequate indices of reliability, with an alpha of 0.83 (Reis et al., 2010).

#### Optimism

Optimism will be assessed with the Life Orientation Test (LOT-R). The LOT-R is a self-report test that uses a Likert scale to measure optimism as a single trait. The test comprises 10 items, with six items formulated positively (items 1, 4, 10) and negatively (items 3, 7, 9), and four distractor items (2, 5, 6, 8). Participants are required to indicate their level of agreement with each item on a 5-point scale, where 1 represents “strongly disagree” and 5 represents “strongly agree.” The total score can range from 6 to 30. To calculate the score, the values of the negative elements are reverse scored and then added to the values of the positive elements, with higher scores indicating greater optimism. The LOT-R was adapted and validated for use in the Brazilian population using a sample of 844 adults and showed adequate internal reliability indices, with an alpha of 0.80 (Bastianello et al., 2014).

#### Hope

Hope will be measured by the Dispositional Adult Hope Scale (DHS), a self-report test consisting of 12 items that measure two dimensions of hope: Agency (4 items) and Means (4 items), with four items as distractors (Snyder et al., 1991). Respondents will rate their agreement with each item on an eight-point Likert scale ranging from 1 (definitely false) to 5 (definitely true). Scores are calculated by adding up the ratings across all items, with higher scores indicating greater levels of hope. A Brazilian adaptation of the DHS was validated using a sample of 844 Brazilian adults and showed adequate indices of reliability, with an alpha of 0.79 (Hutz, 2014).

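### The hope outcome is described inconsistently: the total is summed over all items although four are distractors, and an eight-point response scale is said to run from 1 to 5

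*Protocol article*

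**What the plan says.** The Hope section (Secondary outcomes) describes the Dispositional Adult Hope Scale as "consisting of 12 items that measure two dimensions of hope: Agency (4 items) and Means (4 items), with four items as distractors". On the response format it says: "Respondents will rate their agreement with each item on an eight-point Likert scale ranging from 1 (definitely false) to 5 (definitely true". On scoring it says: "Scores are calculated by adding up the ratings across all items, with higher scores indicating greater levels of hope". It gives no possible range for the total. It reports that the Brazilian adaptation "showed adequate indices of reliability, with an alpha of 0.79", without saying how many items that coefficient covers.

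The Optimism section just before it handles the same feature differently. The LOT-R is described "with six items formulated positively (items 1, 4, 10) and negatively (items 3, 7, 9), and four distractor items (2, 5, 6, 8". Its total is built from the positive and reverse-scored negative items only, and the section adds: "The total score can range from 6 to 30".

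Table 2 shows hope collected at all eight time points, t1 to t8, and Data collection and management says that data are collected through the app. Nothing elsewhere in the article returns to how hope is scored.

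**The concern.** There are two separate contradictions within one paragraph.

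First, the only item total given for the scale is 12, and it includes the distractors. A rule that sums over all items, applied as written, adds four items that the same paragraph does not count towards either dimension of hope. Such items would add variance without adding signal, and the score would no longer be the sum of the items said to measure hope.

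Second, a scale that runs from 1 to 5 in whole steps has five points, not eight. The app has to present one format or the other, and the article does not show which.

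The two differ in how easily they can be repaired. If item-level data are kept, the total can be recomputed later without the distractors, although a change of scoring after the data are seen invites questions about selective definition. A response format built wrongly into the app cannot be corrected once answers have been collected.

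Neither point is detail that an article would leave to a fuller document. The article states a rule and a format, and both conflict with its own description of the instrument.

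**Working it through.** **Step 1: do the neighbouring scales reproduce?** The score range is the number of scored items times the lowest and highest response.

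- LOT-R (Optimism): 6 scored items on 1-5 give 6 × 1 = 6 and 6 × 5 = 30. The stated range of 6 to 30 reproduces, with the distractors excluded. All 10 items would have given 10-50.
- Subjective Happiness Scale (Happiness): 4 items on 1-7 give 4 × 1 = 4 and 4 × 7 = 28. The stated range of 4 to 28 reproduces.

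**Step 2: the hope scale.** Anchors 1 to 5 give 5 points against the stated eight, so the stated number of points does not reproduce. If an eight-point format is taken to run from 1 to 8, the text allows four ranges:

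| Items summed | Responses 1-5 | Responses 1-8 |
|---|---|---|
| All 12 | 12-60 | 12-96 |
| 8 Agency and Means | 8-40 | 8-64 |

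No range is stated that would select one of them.

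**Step 3: what scoring the distractors would cost.** The documents do not supply all the inputs, so this is an illustration. It assumes:

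- alpha 0.79 refers to the 8 hope items;
- all items have equal variance, set to 1;
- the distractors are uncorrelated with the hope items and not moved by treatment.

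Mean inter-item correlation: r = alpha / (k − (k − 1) × alpha) = 0.79 / (8 − 7 × 0.79) = 0.79 / 2.47 = 0.320.

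Variance of the 8-item sum: 8 + 8 × 7 × 0.320 = 25.9.

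Under these assumptions the raw difference between arms is unchanged when the distractors are added. The standardised effect is therefore multiplied by the square root of the variance ratio:

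- Distractors independent of each other: added variance 4, total 29.9, multiplier √(25.9 / 29.9) = 0.93, a loss of about 7%.
- Distractors correlated with each other at 0.32: added variance 4 + 12 × 0.32 = 7.8, total 33.7, multiplier √(25.9 / 33.7) = 0.88, a loss of about 12%.

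**Step 4: the same loss as power.** Take a simple two-group comparison with the planned 100 per condition (Sample size) and two-sided 5% significance. An effect with 80% power on the 8-item score is d = (1.960 + 0.842) / √50 = 0.396. Multiplied by 0.93 or 0.88, power falls to about 74% or 69%. This is only a way to read the size of the dilution. The planned analysis is a mixed model over eight time points, and the trial was not sized on hope.

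**The case against.** The strongest reply is that the wording is loose and the plan is sound. The article speaks of all items and does not write the number 12 in the scoring sentence. A distractor is ordinarily an unscored item, the paragraph assigns only eight items to the two dimensions, and the Optimism section shows that the authors know to leave distractors out. A reader might infer from the scoring sentence that the trial will in fact mis-score hope. The article does not support that: it shows what is written, not what the app or the scoring code computes, and correct scoring in practice is quite possible. This part of the reply stands. What remains is that the literal rule is wrong and nothing in the section corrects it.

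A second reply concerns consequences. Hope is one of four secondary outcomes. The Active control condition section says that the control app has the same structure, including the assessment measures, so whatever format and score are used apply to both arms. A reader might infer a biased comparison or a threat to the main conclusion. Neither follows: the randomised comparison stays valid, and the standardised effect can be estimated under whichever response format is built. This also stands, and it limits the severity.

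A third reply is that the dilution figure rests on assumptions. It does. In particular, if the distractors were related to hope, treatment might move them as well, and the loss would then depend on a model that the documents do not provide. For that reason no figure is offered for that case.

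None of these replies touches the response-scale contradiction, which cannot be read in any consistent way.

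**Conclusion.** The point holds as an internal inconsistency in the definition of a secondary outcome. The response format is impossible as stated, and the scoring rule read literally includes four items that the section itself sets apart as distractors. Together they leave four possible score ranges, so the raw scale on which a hope effect would be reported is not fixed by the article.

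If the distractors were scored, the standardised effect would shrink by roughly 7-12% under the assumptions listed in the working. That is a modest loss of sensitivity on this outcome. The primary PERMA outcome and the stated sample size are untouched. Severity: moderate.

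**What to change.** In the Hope section:

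1. State that the hope total is the sum of the 4 Agency and 4 Means items and that the four distractors are excluded, in the manner already used for the LOT-R.
2. Reconcile the number of response points with the anchors, following the validated Brazilian version that the section cites. The article alone does not show which format that is.
3. Give the resulting range: 8-40 if responses run 1-5, or 8-64 if they run 1-8.
4. Check the app's response options and the scoring code against that statement, if possible before the first participant answers, and keep item-level responses so that the total can be verified.

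The cost is a few words, a possible line of scoring code and one check of the app. Sample size, visit schedule and analysis model stay as they are.
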